## Methods

### Sample size and participants

While the effects of CB tDCS on iTMS have not been previously investigated, the study by Ates and colleagues [18] investigated the influence of CB tDCS on the excitability of the I-wave generating circuits. Consequently, sample size calculations based on this study are sufficient to demonstrate the effects of activation within the pathway of interest (i.e., cerebellar projections to I-wave circuits of M1). Examination of the findings reported by Ates and colleagues revealed that changes in short-interval intracortical facilitation (SICF; paired-pulse TMS protocol indexing I-wave excitability; [22, 23]) due to CB tDCS had an effect size of 0.67. Based on the results of an *a priori* power analysis utilising this effect size, with α = 0.05 and 1-β = 0.9, we will therefore recruit 21 individuals (half female) to participate in the proposed experiment.

All participants will be recruited via advertisements placed on notice boards within the University of Adelaide, in addition to on social media platforms. Exclusion criteria will include a history of psychiatric or neurological disease, current use of medications that effect the central nervous system, or left handedness. Suitability to receive TMS will be assessed using a standard screening questionnaire [24]. The experiment will be conducted in accordance with the Declaration of Helsinki, and has been approved by the University of Adelaide Human Research Ethics Committee (approval H-2019-252). Written, informed consent will be provided prior to participation. Upon completion of the study, all data will be made fully available via hosting on the open science framework repository (https://www.cos.io/osf).

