### Experimental arrangement

All participants will attend the laboratory for three separate sessions, with a washout period of at least 1 week between sessions. While the experimental protocol applied within each session will be the same, the ISI used for iTMS will vary between sessions (see below & Fig 1). Furthermore, the order in which each iTMS interval is applied will be randomised between participants. As diurnal variations in cortisol can influence the neuroplastic response to TMS, all plasticity interventions will be applied after 11 am and at approximately the same time of day within each participant.

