#### I-wave excitability

As assessing the influence of CB modulation on I-wave excitability is the main aim of this project, changes in SICF will be the primary outcome measure. This paired-pulse TMS protocol produces MEP facilitation when conditioning and test stimuli are separated by discrete ISIs that correspond to I-wave latencies recorded from the epidural space [22]. SICF will utilise a conditioning stimulus set at 90% RMT, a test stimulus set at MEP_*1mV*_ and two ISIs of 1.5 and 4.5 ms, which correspond to the early and late MEP peaks apparent in a complete SICF curve [22, 25, 26]. Measurements of SICF will include 12 trials for each condition, at each time point.

As a secondary measure of I-wave function, TMS will be applied with different stimulus directions, which alters the interneuronal circuits contributing to the generated MEP [16, 27, 28]. When TMS is applied with a conventional (PA) current direction, the resulting MEP is thought to arise from preferential activation of early I1-waves. In contrast, when the induced current is directed from anterior-to-posterior (AP; coil handle held 180° to the PA orientation), the resulting MEP is thought to arise from preferential activation of later (I2-3) I-waves. The stimulus intensity producing an MEP of approximately 0.5 mV will be assessed for both PA (MEP_*PA*_) and AP (MEP_*AP*_) orientations at baseline. The same intensities will then be reapplied 5 mins and 30 mins after the intervention, with 20 trials applied at each time point. While the I-wave specificity of these measures is generally suggested to rely on concurrent activation of the target muscle [27], post-intervention muscle activation is also known to strongly influence neuroplasticity induction [29–31]. As the current study is primarily concerned with plasticity induction, these measures will therefore be applied in a resting muscle in order to minimize confounding effects of voluntary contraction. Given the likely independence of the intracortical circuits activated with different currents, these measures will still provide useful physiological insight.

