### Statistical analysis

Kolmogorov-Smirnov tests will be applied to assess data distribution prior to statistical analysis, with log transformation applied when deviations from normal are indicated. Given that all data of interest will involve repeated-measures, linear mixed-model analysis with repeated-measures (LMM_*RM*_) will be used to perform all statistical comparisons. Each model will include single trial data, and previously reported methods [38] will be used to justify inclusion of random participant intercepts and/or slopes, and to optimize and assess model fit. To ensure measures are comparable between sessions, effects of iTMS session (iTMS_*1*.*5*_, iTMS_*4*.*5*_ & iTMS_*Sham*_) on baseline measures of MEP_*1mv*_, MEP_*PA*_, MEP_*AP*_ and CBI, in addition to responses recorded at the start of the iTMS intervention, will be investigated using one-factor LMM_*RM*_, with each measurement investigated in a separate model. Furthermore, effects of iTMS session and ISI (1.5 & 4.5 ms) on baseline SICF will be assessed using two-factor LMM_*RM*_.

Changes in excitability during the intervention will be assessed by comparing values averaged over the first, middle and last 12 stimuli of the iTMS block between iTMS sessions. Changes in corticospinal excitability following the intervention will be investigated by assessing the effects of iTMS session and time (Post 5, Post 30) on baseline-normalised MEP_*1mV*_ values. Changes in coil-orientation dependent measures of I-wave excitability following the intervention will be investigated by assessing effects of iTMS session, time and coil orientation (MEP_*PA*_, MEP_*AP*_) on baseline-normalised values. Changes in SICF measures of I-wave excitability following the intervention will be investigated by assessing effects of iTMS session, time and ISI on baseline-normalised values. Changes in CBI following the intervention will be investigated by assessing the effects of iTMS session and time on baseline-normalised CBI values. For all models, investigation of main effects and interactions will be performed using custom contrasts with Bonferroni correction, and significance will be set at *P* < 0.05. Data for all models will be presented as the estimated marginal means, whereas pairwise comparisons will be presented as the estimated mean difference (EMD) and 95% confidence interval (95%CI) for the estimate, providing a non-standardised measure of effect size.

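### Visit number is in none of the listed outcome models of this three-session crossover; the cost is precision, not systematic bias

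*Protocol article*

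**What the plan says.** **Design.** Experimental arrangement describes a within-participant crossover: "three separate sessions, with a washout period of at least 1 week between sessions", in which "the order in which each iTMS interval is applied will be randomised between participants". No allocation scheme (simple, blocked or Latin square) is named. Sample size and participants sets the number: "we will therefore recruit 21 individuals (half female").

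**Primary outcome.** Under I-wave excitability, "changes in SICF will be the primary outcome measure". The SICF model works by "assessing effects of iTMS session, time and ISI on baseline-normalised values".

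**Other models.** MEP1mV and CBI use session and time. The coil-orientation measure uses session, time and orientation. Time is spelled out as "time (Post 5, Post 30"), so it is the assessment point within a session and not the visit.

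**Related safeguards.** Data analysis expresses each post-intervention response as a percentage of the pre-intervention one. The Statistical analysis section compares baselines across iTMS sessions, but not across visits. Its model-building step deals with random participant intercepts and slopes and with model fit; it mentions no visit term.

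**The concern.** In a three-period crossover, period is a standard nuisance factor. If people respond differently to the intervention on their first exposure than on later ones, that variation has to go somewhere. With visit in the model it is removed. Without it, it enters the within-participant error. In addition, if the three conditions did not fall equally often at the first visit, part of it enters the estimated difference between conditions in that sample.

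The stake is the sensitivity of the iTMS session comparisons, including the primary SICF comparison, in a study of only 21 people. The plan already guards against one nuisance influence on plasticity by holding time of day roughly constant within a participant. Visit number is a comparable influence and gets no such treatment.

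**Working it through.** **1. The plan's own figure.** Inputs from Sample size and participants: SICF changes "due to CB tDCS had an effect size of 0.67", "with α = 0.05 and 1-β = 0.9". For a paired t-test with n = 21 the noncentrality is 0.67 × √21 = 3.07.
- One-sided, α = 0.05: power 90.6% at n = 21, so 21 is reproduced.
- Two-sided, α = 0.05: power 83.1% at n = 21, and 26 would be needed for 90%.

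Sidedness is not stated. The visit question does not change the 21. Two-sided tests are used below.

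**2. Bias in expectation.** Under independent draws from the six possible orders, each condition comes first with probability 1/3. The expected difference between two conditions in first-visit share is therefore 0 (simulated: 0.000). Simulated contrast estimates average 0.668 to 0.670 against a true 0.67.

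**3. Chance imbalance, if orders are drawn independently.** The indicator difference (condition A first minus condition B first) has variance 2/3 per person.
- SD of the count difference: √(21 × 2/3) = √14 = 3.74 people, or 3.74/21 = 0.178 of the sample.
- Simulated 95% range: −7 to +7 people. A gap of 5 or more for a given pair of conditions occurs in 23% of lists. Exact 7/7/7 at the first visit occurs in 3.9%.
- A gap of 7 shifts that contrast by 7/21 = one third of the first-visit effect.

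**4. Precision.** Let g be the first-visit effect in SDs of the paired session difference. This is an assumption, since the documents give no value. The variance of one person's contrast is 1 + (2/3)g², so the SD of the mean contrast is √[(1 + 2g²/3)/21]. Simulation: 10,000 trials per row, one session contrast, d = 0.67.

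| g | SD by formula | SD simulated | Type I error, no visit term | Power, no visit term | Power, visit term |
|---|---|---|---|---|---|
| 0 | 0.218 | 0.215 | 4.6% | 83.7% | 83.1% |
| 0.25 | 0.223 | 0.219 | 4.5% | 81.9% | 83.1% |
| 0.5 | 0.236 | 0.232 | 4.5% | 77.6% | 83.1% |
| 1.0 | 0.282 | 0.279 | 4.8% | 61.5% | 83.1% |

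Type I error with the visit term is 4.4%.

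**5. Does balance alone help?** With each condition 7 times at each visit but no visit term, power is 78.5% at g = 0.5 and 63.7% at g = 1.0, little better than in step 4. Type I error falls to 3.1% and 1.2%: the contrast is now free of the visit effect, but its error estimate is not. With balance and the visit term, power is 84.6%.

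**6. Price of the term when g = 0.** From the table, 83.7 − 83.1 = 0.6 points. That sets a paired t-test (20 df) against a regression pooling all three sessions (63 − 21 − 4 = 38 df). The pooled regression without visit has 63 − 21 − 2 = 40 df and, by noncentral t, 85.0% power. Like for like, the price is 85.0 − 83.1 = 1.9 points. A further 8,000 simulated trials gave 84.6% against 82.9%, or 1.7 points. In those runs the pooled model without visit gave about 83%, 79% and 63% at g = 0.25, 0.5 and 1.0, so the term roughly breaks even at 0.25 and gains clearly above that.

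**The case against.** Much of the case on the other side stands.

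- **Bias.** A reader might infer that visit effects systematically distort the session contrasts. Randomised order rules that out in expectation, and steps 2 and 4 agree.
- **Unbalanced orders.** A reader might also infer that the orders are unbalanced. The article does not say so. It names no scheme, and a condensed article may leave that to the full protocol. Nor is 21 an obstacle: six orders cannot be filled equally, but each condition can still occur 7 times at each visit.
- **Practice.** Learning over visits is not a supported mechanism. The outcomes are evoked responses in resting muscle, and no motor task is described.
- **Normalisation.** Threshold and the 1 mV intensity are set anew each session, and outcomes are relative to that session's baseline. Much of any visit-to-visit shift in level therefore cancels. Only a visit effect on the response to the intervention remains, and nothing in the documents shows that one exists or how large it is.
- **Scale.** At 0.25 SD the loss is under 2 points, and the Introduction calls the study exploratory.

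What these points do not answer is that the factors of the outcome models are listed and visit is not among them. That is a stated analysis choice, and it can be improved at little cost.

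**Conclusion.** The point holds as a modest one about efficiency. The session-comparison models should carry visit number and, as listed, do not. Validity is not threatened: the contrasts are unbiased over randomisation and type I error stays near 5%.

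The loss depends wholly on an effect the documents do not quantify. It is nil if visit does not alter the response, about 6 points of two-sided power at 0.5 SD (83.7 − 77.6) and about 22 points at 1.0 SD (83.7 − 61.5). The visit term holds power at about 83% in every case.

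These figures assume independent draws of order, an effect confined to the first visit, one summary value per session, equal variances, and a single two-sided contrast at d = 0.67 without Bonferroni correction. They show the pattern; they do not forecast the power of the planned single-trial mixed models.

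**What to change.** Add visit number (1, 2, 3) as a categorical fixed factor in every model that compares iTMS sessions: MEP1mV, coil orientation, SICF, CBI, the response during iTMS and the baseline checks. The cost is 2 degrees of freedom and, if there is no visit effect, about 0.6 points of power against a paired t-test, or just under 2 points against the same pooled model without the term.

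Optionally, state the allocation scheme and use a prepared list that places each condition 7 times at each visit. Three copies of all six orders (18 people) plus one three-order Latin square (3 people) gives 21. A three-order Latin square used 7 times does the same. The list is a small addition that makes the visit term nearly free (84.6% power with both). It does not replace the term, because balance without it recovers almost no power.

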**Fig 1 pone.0236005.g001:**

Experimental protocol. RMT, resting motor threshold; MEP_*1mV*_, standard MEP of ~ 1 mV at baseline; CBI, cerebellar-brain inhibition; SICF, short-interval intracortical facilitation; MEP_*PA*_, standard MEP of ~ 0.5 mV at baseline with PA orientation; MEP_*AP*_, standard MEP of ~ 0.5 mV at baseline with AP orientation; tDCS_*CB*_, transcranial direct current stimulation applied to the cerebellum; iTMS, I-wave periodicity repetitive transcranial magnetic stimulation.

During each experimental session, the participant will be seated in a comfortable chair with their hand resting on a table in front of them. Surface electromyography (EMG) will be recorded from the first dorsal interosseous (FDI) of the right hand using two Ag-AgCl electrodes arranged in a belly-tendon montage on the skin above the muscle. A third electrode attached above the styloid process of the right ulnar will ground the electrodes. EMG signals will be amplified (300x) and filtered (band-pass 20Hz– 1 kHz) using a CED 1902 signal conditioner (Cambridge Electronic Design, Cambridge, UK) before being digitized at 2 kHz using CED 1401 analogue-to-digital converter and stored on a PC for offline analysis. Signal noise associated with mains power (within the 50 Hz frequency band) will also be removed using a Humbug mains noise eliminator (Quest Scientific, North Vancouver, Canada). To facilitate muscle relaxation when required, real-time EMG signals will be displayed on an oscilloscope placed in front of the participant.

### Experimental procedures

#### Transcranial magnetic stimulation (TMS)

A figure-of-8 coil connected to two Magstim 200^2^ magnetic stimulators (Magstim, Dyfed, UK) via a BiStim unit will be used to apply TMS to the left M1. The coil will be held tangentially to the scalp, at an angle of 45° to the sagittal plane, with the handle pointing backwards and laterally, inducing a posterior-to-anterior (PA) current within the brain. The location producing the largest and most consistent motor evoked potential (MEP) within the relaxed FDI muscle of the right hand will be identified and marked on the scalp for reference; this target location will be closely monitored throughout the experiment. All pre- and post-intervention TMS will be applied at a rate of 0.2 Hz, with a 10% jitter between trials in order to avoid anticipation of the stimulus.

Resting motor threshold (RMT) will be defined as the stimulus intensity producing an MEP amplitude ≥ 50 μV in at least 5 out of 10 trials during relaxation of the right FDI. RMT will be assessed at the beginning of each experimental session and expressed as a percentage of maximum stimulator output (%MSO). Following assessment of RMT, the stimulus intensity producing a standard MEP amplitude of approximately 1 mV (MEP_*1mV*_), when averaged over 20 trials, will be identified. The same intensity will then be applied 5 mins and 30 mins following the intervention in order to assess changes in corticospinal excitability.

#### I-wave excitability

As assessing the influence of CB modulation on I-wave excitability is the main aim of this project, changes in SICF will be the primary outcome measure. This paired-pulse TMS protocol produces MEP facilitation when conditioning and test stimuli are separated by discrete ISIs that correspond to I-wave latencies recorded from the epidural space [22]. SICF will utilise a conditioning stimulus set at 90% RMT, a test stimulus set at MEP_*1mV*_ and two ISIs of 1.5 and 4.5 ms, which correspond to the early and late MEP peaks apparent in a complete SICF curve [22, 25, 26]. Measurements of SICF will include 12 trials for each condition, at each time point.

As a secondary measure of I-wave function, TMS will be applied with different stimulus directions, which alters the interneuronal circuits contributing to the generated MEP [16, 27, 28]. When TMS is applied with a conventional (PA) current direction, the resulting MEP is thought to arise from preferential activation of early I1-waves. In contrast, when the induced current is directed from anterior-to-posterior (AP; coil handle held 180° to the PA orientation), the resulting MEP is thought to arise from preferential activation of later (I2-3) I-waves. The stimulus intensity producing an MEP of approximately 0.5 mV will be assessed for both PA (MEP_*PA*_) and AP (MEP_*AP*_) orientations at baseline. The same intensities will then be reapplied 5 mins and 30 mins after the intervention, with 20 trials applied at each time point. While the I-wave specificity of these measures is generally suggested to rely on concurrent activation of the target muscle [27], post-intervention muscle activation is also known to strongly influence neuroplasticity induction [29–31]. As the current study is primarily concerned with plasticity induction, these measures will therefore be applied in a resting muscle in order to minimize confounding effects of voluntary contraction. Given the likely independence of the intracortical circuits activated with different currents, these measures will still provide useful physiological insight.

#### Cerebellar-brain inhibition (CBI)

The strength of CB’s inhibitory influence on M1 will be assessed using CBI, a stimulation protocol involving a conditioning stimulus applied to CB 5 ms prior to a test stimulus applied to M1 [5]. In accordance with previous literature, CB stimulation will be applied using a double cone coil, with the center of the coil located 3 cm lateral and 1 cm inferior to the inion, along the line joining the inion and the external auditory meatus of the right ear. The coil current will be directed downward, resulting in an upward induced current. The intensity of CB stimulation will be set at 60% MSO [32], whereas M1 stimulation will be set at MEP_*1mV*_. The dual coil configuration of this measurement will mean that each coil will be directly connected to an individual Magstim 200^2^ stimulator. As removing the BiStim unit will result in an increase in stimulus strength, the MEP_*1mV*_ intensity will be checked prior to baseline CBI measures, and adjusted when required. Because antidromic activation of corticospinal neurons may confound measures of CBI [33], we will ensure that the CB conditioning stimulus is at least 5% MSO below the active motor threshold for the corticospinal tract [34]. Measures of CBI will be assessed at baseline, 5 mins and 30 mins post-intervention, with 15 trials recorded for each condition at each time point.

#### I-wave periodicity repetitive TMS (iTMS)

In accordance with previous literature [21, 35], iTMS will consist of 180 pairs of stimuli applied every 5 s, resulting in a total intervention time of 15 mins. The same intensity will be used for both stimuli, adjusted to produce a response of ~ 1mV when applied as a pair. These stimuli will be applied using ISI’s of 1.5 (iTMS_*Early*_) and 4.5 ms (iTMS_*Late*_) in separate sessions. These parameters produce robust potentiation of MEP amplitude [20, 21, 35, 36]. A sham stimulation condition (iTMS_*Sham*_) that is not expected to modulate corticospinal excitability will also be applied in a third session. Within this condition, we will stimulate intervals that correspond to the transition between the peaks and troughs of facilitation that are observed within a complete SICF curve, as these are not expected to induce any changes in excitability. This will include equal repetitions of 1.8, 2.3, 3.3, 3.8 and 4.7 ms ISI’s, applied randomly and with an inter-trial jitter of 10%.

#### Cerebellar transcranial direct current stimulation (tDCS_CB_)

A Soterix Medical 1 x 1 DC stimulator (Soterix Medical, New York, NY) will be used to apply tDCS to CB. Current will be applied through saline-soaked sponge electrodes (EASYpads, 5 x 7 cm), with the cathode positioned over the same location used for CB TMS (i.e., 3 cm lateral and 1 cm inferior to inion, contralateral to M1 TMS) and anode positioned on the skin above the right Buccinator muscle [4, 13, 37]. Stimulation will be applied at an intensity of 2 mA for 15 mins [4, 13, 37], coincident with the application of iTMS to M1. Onset and offset of stimulation will be ramped over a 30 s period prior to and following iTMS application.

### Data analysis

Analysis of EMG data will be completed manually via visual inspection of offline recordings. For measures in resting muscle, any trials with EMG activity exceeding 25 μV in the 100 ms prior to stimulus application will be excluded from analysis. All MEPs will be measured peak-to-peak and expressed in mV. Measures of CBI will be quantified by expressing the amplitude of individual trials produced by paired-pulse stimulation as a percentage of the mean response produced by single-pulse stimulation within the same block. For baseline measures of SICF, individual trials produced by paired-pulse stimulation will be expressed as a percentage of the mean response produced by single-pulse stimulation within the same block. However, for post-intervention responses, previous work has suggested that increased facilitation following iTMS correlates with the increased response to single pulse stimulation, and that this relationship cancels the effects of iTMS on SICF if the post-intervention single-pulse MEPs are used to normalise post-intervention SICF values [21]. Consequently, prior to normalization of post-intervention SICF values, we will use linear regression analysis to assess the relationship between post-intervention single and paired-pulse responses. If the relationship is significant, individual post-intervention SICF trials will be expressed relative to the mean pre-intervention single-pulse MEP [21]. However, if the relationship is not significant, post-intervention SICF measures will be expressed relative to the single-pulse response recorded in the same block. For all TMS measures, effects of the intervention will be quantified by expressing the post-intervention responses (normalised to the relevant single-pulse response for CBI and SICF) as a percentage of the pre-intervention responses.

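### Two numerical scoring rules are applied by eye to digitised traces; scripting the same rules would remove avoidable judgement from the primary SICF comparison at little cost

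*Protocol article*

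**What the plan says.** The Data analysis section names the method: "Analysis of EMG data will be completed manually via visual inspection of offline recordings". For resting-muscle measures, "any trials with EMG activity exceeding 25 μV in the 100 ms prior to stimulus application will be excluded from analysis", and "All MEPs will be measured peak-to-peak and expressed in mV". Experimental arrangement says that the EMG is digitised at 2 kHz and stored on a PC.

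These scores carry the main result. Under I-wave excitability, "changes in SICF will be the primary outcome measure" and "Measurements of SICF will include 12 trials for each condition, at each time point". Under Statistical analysis, "Each model will include single trial data", and "Changes in SICF measures of I-wave excitability following the intervention will be investigated by assessing effects of iTMS session, time and ISI", using values normalised to baseline. Sessions differ in one planned respect: "the ISI used for iTMS will vary between sessions". The SICF intervals themselves, 1.5 and 4.5 ms, are the same in every session.

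The article does not say whether the person scoring knows the session or time point. It describes neither automated scoring nor a second reader.

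**The concern.** Both rules have an exact numerical answer on a stored digital trace, yet the plan assigns them to visual inspection. Two decisions then rest on judgement: whether a trial close to 25 μV is kept, and where the peak and trough cursors go.

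The plan states its expectations by session. The section on iTMS expects potentiation with the 1.5 and 4.5 ms intervals and no change with sham. If judgement drifted with those expectations after the intervention, the scores would carry a difference in the same direction as the effect being tested. The mixed model works on the scored values and could not separate the two. Random scoring error would only add noise. A systematic error that follows session and time would not average out over participants.

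**Working it through.** The plan gives no figure for scoring error, so there is no stated value to reproduce. The check covers what can be computed, which scoring errors survive the planned analysis, how many traces are involved, and how sensitive a cell and a contrast would be.

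**1. Can the rules be computed?** At 2 kHz, the 100 ms window holds 0.100 × 2,000 = 200 samples. Exceeding 25 μV in those samples, and maximum minus minimum in a window after the stimulus, are both direct calculations.

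**2. Which scoring errors survive?** Write the scored mean in session *s* at time *t* as the true mean × a(s) × b(t) × c(s,t). Here a is a proportional tendency constant within a session, b is one common to all sessions at a given time, and c is one that depends on both. The planned outcome is post divided by pre:

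(true post / true pre) × [b(post)/b(pre)] × [c(s,post)/c(s,pre)]

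- a(s) cancels. This holds for SICF under either normaliser in Data analysis (pre-intervention or same-block single-pulse mean).
- b(post)/b(pre) is the same in every session. It cancels on the log scale. On the percentage scale it rescales all sessions alike and cannot create a session difference.
- c(s,t) remains. Only this component can bias the session comparison.

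**3. How many traces?** Trials per time point, from the measure descriptions:

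| Measure | Trials |
|---|---|
| MEP at 1 mV | 20 |
| MEP, PA orientation | 20 |
| MEP, AP orientation | 20 |
| SICF: 12 × 3 (two ISIs plus single pulse, assumed) | 36 |
| Cerebellar-brain inhibition: 15 × 2 (paired plus single pulse, assumed) | 30 |
| Total | 126 |

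- Test traces: 126 × 3 time points × 3 sessions × 21 participants = 23,814.
- iTMS traces analysed: first, middle and last 12 stimuli, so 36 × 3 × 21 = 2,268.
- Total: 23,814 + 2,268 = 26,082, roughly 26,100.
- SICF only: 21 × 3 × 3 × 12 × 2 = 4,536 paired-pulse traces, or 21 × 3 × 3 × 12 × 3 = 6,804 with the single-pulse condition.

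**4. What does one decision do in a 12-trial cell?** Suppose one trial lies 50% above its cell mean (assumption). Dropping it changes the mean from 12/12 = 1 to (12 − 1.5)/11 = 10.5/11 = 0.955, a fall of 4.5%. If the cell is the single-pulse mean used as denominator, every SICF value in that block rises by 11/10.5 = 1.048, or 4.8%. This describes one decision in one cell, not an average over the study.

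**5. How sensitive is a session contrast?** Take one contrast as a paired t test with n = 21 and two-sided 0.05, a simplification of the mixed model. Assume a systematic shift of the surviving kind, in SDs of the within-participant difference between two sessions:

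| Assumed shift (SD) | False-positive rate |
|---|---|
| 0.05 | 5.5% |
| 0.1 | 7.2% |
| 0.2 | 14.1% |
| 0.3 | 25.8% |

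Nothing in the documents says where in this range, if anywhere, the study would fall.

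**The case against.** The case for leaving the plan alone is substantial. The threshold, the window and the amplitude definition are all fixed in advance. Manual inspection need not mean that amplitudes are guessed, since cursors can be placed on a digital trace, and peak-to-peak leaves little latitude once the response is located. The post/pre ratio removes the simplest forms of scoring tendency. Baseline measures, SICF included, are compared between sessions. The study calls itself exploratory and commits to making all data available. All of this stands and limits the size of the point. It does not remove it: a baseline comparison cannot reveal a tendency that appears only after the intervention in some sessions.

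A reader might infer more than the documents support, in four ways:

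- **That the scorer knows the session.** Masking is neither stated nor denied, and an article may leave it to the full protocol. A masked manual scorer would add noise but no session-related bias. The point rests on the stated choice of manual scoring, not on that silence.
- **That the traces give the session away.** File naming is not described. The test MEP is set to about 1 mV in each session, iTMS pairs are adjusted to about 1 mV in each condition, and the SICF intervals do not change. Trace size at baseline should therefore not reveal the session.
- **That any session-related tendency biases the result.** Step 2 shows that only one varying by session and time together does.
- **That every iTMS pair is scored.** Counting all 180 pairs gives 180 × 3 × 21 = 11,340 traces and a total of 35,154. Statistical analysis uses only 36 stimuli per session.

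**Conclusion.** The point holds as a cheap improvement to a stated method. It is not a demonstrated error, and it is not evidence of bias. The plan assigns two computable rules to the eye, which leaves borderline exclusions and cursor placement to judgement in 12-trial SICF cells. That judgement could bias the primary session contrast only if it differs by session and time point jointly.

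The amount of bias cannot be derived from the documents. The cell shifts and false-positive rates above show sensitivity under assumed inputs and estimate nothing about this study. The trace counts rest on the stated trial numbers and on counting single-pulse trials as one condition in SICF and in cerebellar-brain inhibition.

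The change is worth making because the planned analysis could not detect or correct such a bias afterwards, while prevention is simple before scoring starts.

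**What to change.** Keep both rules and change how they are applied:

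- Compute peak-to-peak amplitude by script in a fixed post-stimulus window, set before scoring, and apply the 25 μV, 100 ms rule by the same script to all resting trials.
- Limit visual review to traces that the script flags, for example for artefact. Replace session and time-point labels with codes until scoring is locked.
- Report the number of excluded trials by session and time point.

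Coded review is feasible for the pre- and post-intervention blocks, which use the same SICF intervals in every session. For traces recorded during iTMS the stimulus interval itself may reveal the session, so protection there comes from the script.

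The cost is a short script and recoded files. Some flagged traces will still need to be looked at. No extra assessor is needed, and the sample size, the model and the participants' procedures do not change. The fix addresses scoring only. It does not protect against session-related differences in acquisition, such as coil placement or intensity setting.
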